### Statistical analysis

A descriptive analysis of the variables recorded will be performed. Observed frequencies and percentages will be used for qualitative variables, with their 95% confidence interval, and the mean and standard deviation or median and interquartilic range for quantitative variables.

The primary outcome for this study will be the estimation of the probability of cardiovascular disease in the presence of other competitive events in renal transplant patients. The cumulative incidence of cardiovascular events after kidney transplantation will be analyzed by competing risk survival methods, where each subject is at risk of failure from different causes. Therefore, each patient will be classified in four states of interest (alive with functioning graft, death, graft failure and cardiovascular disease).

Cumulative incidence functions will be used to compare the observed incidence of events between groups [48]. The cumulative incidence function regression model of Fine and Gray will be used for multiple regression analyses [49]. Additionally, the clinical relevance of different variables will be evaluated using the ARR (Absolute Risk Reduction), RRR (Relative Risk Reduction) and NNT (Number Needed to Treat).

In order to analyze the ability of each of the four cardiovascular risk scores to predict cardiovascular events rates, the concordance c index [50] and the area under the receiver-operating characteristic (ROC) curves, using a time-dependent approach [51], will be calculated. To calibrate the scores, relative risk ratios for observed-to-predicted event rates will be computed, and the Hosmer-Lemeshow test will be applied.

Based on the competing risks analysis, a nomogram to estimate the probability of cardiovascular events after kidney transplantation will be developed. The objective is to use the conditional cumulative incidence function to provide a patient-specific prediction of the probability of failure in the setting of competing risks.

The predictive performance of the nomogram will be evaluated by assessing both discrimination and calibration values [52]. A bootstrap re-sampling approach with 1000 replications will be used to reduce overfit bias. Discrimination will be quantified with the concordance c index and the area under the receiving operating characteristic (ROC) curve [50,51]. The nomogram will then be calibrated graphically, comparing the predicted probabilities with the actual rate of patients with cardiovascular events. A Loess curve will be fitted to the data and compared with an ideal fit. In addition, the Brier score will be calculated as a measure of the predictive accuracy of the model.

A p-value of < 0.05 will be considered as statistically significant (two-sided). Statistical analyses will be carried out with SPSS version 17.0 (SPSS Inc., Chicago, IL.) and R version 2.9.1 (The R Foundation for Statistical Computing), adding the ROCR, Design and Hmisc libraries.

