## Background

Cardiovascular disease (CVD) is one of the most common complications after renal transplantation, with a considerably higher incidence than in the general population [1]. Although in recent years some authors have documented a significant reduction in cardiovascular death after kidney transplantation [2], today CVD is still the major known cause of death in kidney transplant patients [3].

In addition to the conventional CVD risk factors (such as obesity, smoking habits, diabetes, hypertension or dyslipidemia), several other factors seem to influence the high incidence of cardiovascular events in renal transplant patients [4,5]. These include, amongst others, the duration of prior dialysis [6-8], graft function after transplantation [9-11], hyperhomocysteinemia [12-16], elevated inflammatory markers [16-18], proteinuria [19-22], acute rejection episodes [23], post-transplant diabetes mellitus [6,24-27], and the toxic effects derived from the use of immunosuppressant medications and other drugs [28,29].

Therefore, when evaluating patients prior to kidney transplantation, special attention should be given to cardiovascular risk factors. To determine the individual risk of cardiovascular events, risk scores have been established in general populations, such as the Framingham Heart Study score [30,31], the Regicor (Framingham calibrated to Spain) [32], SCORE [33] or DORICA [34]. However, the validity of these equations in more selected populations, such as those of transplant patients, is not well established. In renal transplant recipients, the Framingham score does not seem to accurately predict the individual cardiovascular risk, leading to an underestimation of the cardiovascular event rates [4,16]. A recent study has corroborated the poor predictive accuracy of the Framingham score in these patients, indicating the need to consider new predictive models that incorporate both traditional and non-traditional cardiovascular risk factors [35].

Determining the incidence of cardiovascular events after a kidney transplant and the associated risk factors is therefore important in order to inform physicians of the need for CVD screening and prevention as part of the transplant evaluation [36]. Moreover, an accurate estimation of a patient's risk of cardiovascular disease could make it possible to identify people at high risk of suffering a cardiovascular event, and intervene proactively before they develop the disease.

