For the analysis, the cut-points defining the control of each risk factor will be taken from the European Guidelines on CVD prevention [39]. For estimates of dyslipidemia control based on LDL, HDL cholesterol and triglycerides, we will use the cut-points agreed in the consensus statement from the American Diabetes Association and the American College of Cardiology Foundation [40].

The initial immunosuppressive regimen of the patients and changes in treatment during follow-up will be recorded. Dosage of immunosuppressive drugs will also be registered after transplantation at week 1, week 2, months 1, 3 and 6, and yearly thereafter. The use of antihypertensive and lipid-lowering drugs after transplantation will also be registered at the same times.

Post-transplant cardiovascular events are defined as the presence of myocardial infarction, invasive coronary artery therapy, cerebral vascular events (stroke and transient ischemic attacks), new-onset angina, congestive heart failure, rhythm disturbances (ventricular tachycardia, atrial fibrillation and the need for a pacemaker), and peripheral vascular disease. Peripheral vascular disease is defined as the need for invasive therapy or conservatively managed limb gangrene.

Patients will be followed-up from the date of renal transplantation until death or their return to dialysis.

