### Quantification of cardiovascular risk

Four established cardiovascular risk scores will be applied to the kidney transplant recipients at the time of transplantation: the Framingham risk factor score, the European Systematic Coronary Risk Evaluation (SCORE) equation, and two coronary risk equations that use the calibrated Framingham functions for the Spanish population, the REGICOR (Registre Gironí del COR (Gerona Heart Registry)) and DORICA (Dyslipidemia, Obesity, and Cardiovascular Risk) functions.

The Framingham risk score will be calculated using both the classic Framingham-Anderson equation [30] and the equation modified by Wilson [31]. These scores predict the risk of developing fatal or non-fatal coronary heart disease (CHD) within a 10-year time period in adults between the ages of 30-74 with no known previous history of CHD, stroke, or peripheral vascular disease. CHD includes angina pectoris, myocardial infarction, coronary insufficiency (unstable angina) and coronary heart death.

The original Framingham-Anderson equation includes the following risk factors: age, sex, systolic blood pressure, total cholesterol, HDL-cholesterol, diabetic status, tobacco smoking status and evidence of left ventricular hypertrophy on resting electrocardiogram (ECG). The Framingham-Wilson equation replaces the continuous measurements of systolic blood pressure, total cholesterol and HDL-cholesterol with categorical variables based on the risk categories of the Joint National Committee on Blood Pressure and the National Cholesterol Education Program (NCEP) [41-43]. It also takes into account information regarding diastolic and LDL-cholesterol levels, and does not include the diagnosis of left ventricular hypertrophy due to its high association with hypertension and the absence of standard, universally accepted ECG criteria.

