The European SCORE was developed by the European Society of Cardiology in 2003 as an estimation of 10-year risk of fatal cardiovascular disease (CVD) in subjects between the ages of 24 and 80. The variables used to calculate this score include age, gender, total cholesterol, systolic blood pressure and current smoking status [33]. The main difference between the SCORE risk chart and the Framingham model is that it estimates the risk for all atherothrombotic cardiovascular manifestations, including stroke, heart failure, peripheral arterial insufficiency or certain aneurysms, and not just CHD. The SCORE charts are currently the CVD charts recommended by the European Societies [44] and the Spanish Interdisciplinary Committee for Cardiovascular Disease Prevention (CEIPC) [45]. The SCORE risk charts calibrated for Spain will be used [46].

Finally, the REGICOR [32] and the DORICA [34] charts are adaptations of the Framingham equation to the Spanish population characteristics. Like the Framingham equation, these functions estimate the risk of coronary mortality and morbidity using information about age, gender, total cholesterol, HDL-cholesterol, systolic and diastolic blood pressure and smoking habits, differentiating diabetic from non-diabetic patients.

Patients will be classified as high-risk patients when their ten-year risk of coronary heart disease is ≥20% according to Framingham [31], REGICOR [32] and DORICA [34] equations or when their ten-year risk of cardiovascular mortality is ≥5% according to the SCORE system [44].

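### A cardiovascular death with no documented listed event is counted as a competing event, because the event list omits cardiovascular death and the death state is not split by cause

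*Protocol article*

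**What the plan says.** The Measurements section of the protocol article defines the outcome by enumeration. It opens "Post-transplant cardiovascular events are defined as the presence of myocardial infarction, invasive coronary artery therapy, cerebral vascular events" (stroke and transient ischaemic attack) and continues "new-onset angina, congestive heart failure, rhythm disturbances (ventricular tachycardia, atrial fibrillation and the need for a pacemaker), and peripheral vascular disease". The Abstract (Methods/Design) gives a matching list and puts patient survival beside it as a separate follow-up event. Neither list contains cardiovascular, coronary or sudden cardiac death.

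The Statistical analysis section states the primary outcome as "the estimation of the probability of cardiovascular disease in the presence of other competitive events in renal transplant patients". For that analysis "each patient will be classified in four states of interest (alive with functioning graft, death, graft failure and cardiovascular disease". Death appears there once, with no cause attached. On modelling, "The cumulative incidence function regression model of Fine and Gray will be used for multiple regression analyses". Nothing else in the article moves a cardiovascular death into the cardiovascular disease state.

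The Background motivates the study by noting that "CVD is still the major known cause of death in kidney transplant patients", and the Discussion says the same of patients with a functioning graft.

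The scores to be validated all cover fatal events. Under Quantification of cardiovascular risk, SCORE is described "as an estimation of 10-year risk of fatal cardiovascular disease (CVD) in subjects between the ages of 24 and 80". For Framingham, "CHD includes angina pectoris, myocardial infarction, coronary insufficiency (unstable angina) and coronary heart death". REGICOR and DORICA are said to estimate coronary mortality as well as morbidity.

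**The concern.** In a competing-risks analysis, an event placed in a competing state is treated as something that stops the outcome from happening. A cardiovascular death with no recorded listed event is itself the disease under study, in its most severe form. The plan as written nevertheless places it with deaths from infection or cancer.

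Three results are exposed:

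- **Cumulative incidence.** The primary estimate loses these patients, so it understates total post-transplant cardiovascular disease.
- **Fine and Gray regression and the nomogram.** A factor that raises fatal cardiovascular risk more than non-fatal risk has part of its effect moved to the competing side.
- **Score calibration.** Observed-to-predicted ratios would compare predictions that include fatal events with an observed count from which some fatal events have been removed.

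**Working it through.** **1. Which deaths are affected.** Set the event list against the four states.

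| Patient history | State under the plan |
|---|---|
| Any listed event, later death from any cause | Cardiovascular disease (first event) |
| Death from a documented infarction, stroke, heart failure or ventricular tachycardia | Cardiovascular disease; no component is restricted to non-fatal events |
| Sudden cardiac or other cardiovascular death, no listed event recorded | Death, i.e. competing |
| Non-cardiovascular death, no listed event | Death, i.e. competing |

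Only the third row is misplaced.

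**2. The plan's own figure.** Sample size section: relative risk 1.33, exposure 50%, 78% censored, two-sided 0.05, power 80%.

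- Events = (1.960 + 0.842)² / (0.25 × ln(1.33)²) = 386.04.
- N = 386.04 / 0.22 = 1754.7, i.e. 1755.

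The stated 1755 is reproduced and is not in dispute. Adding cardiovascular deaths could only add events.

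**3. Effect on incidence.** The article gives no rate for the third row, so the share x of patients dying this way by five years is assumed. The stated five-year incidence is 22.2% and the cohort is 1794 patients. It is further assumed that the 22.2% excludes such deaths. Incidence with these deaths included = 22.2% + x. Relative understatement = 1 − 22.2/(22.2 + x). Patients moved = 1794 × x.

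| x (assumed) | Incidence | Relative understatement | Patients |
|---|---|---|---|
| 1% | 23.2% | 4% | 18 |
| 2% | 24.2% | 8% | 36 |
| 3% | 25.2% | 12% | 54 |
| 5% | 27.2% | 18% | 90 |

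**4. Effect on the subdistribution hazard ratio.** This is an illustration with assumed constant hazards: listed events 0.05 per year (hazard ratio 1.33 for the factor), other competing events 0.02 per year (no effect of the factor), and cardiovascular death without a listed event at hazard d per year. With outcome hazard a and competing hazard b:

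- Incidence by time t = a/(a + b) × (1 − exp(−(a + b)t)), with t = 5.
- Approximate subdistribution hazard ratio = ln(1 − incidence in exposed) / ln(1 − incidence in unexposed).

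Worked case, d = 0.002, hazard ratio 2.0 for that death, deaths competing:

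- Unexposed: a = 0.05, b = 0.022, incidence 0.2099.
- Exposed: a = 0.0665, b = 0.024, incidence 0.2674.
- Ratio = ln(0.7326)/ln(0.7901) = 1.32.

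| d per year | Hazard ratio for that death | Deaths competing | Deaths counted as outcome |
|---|---|---|---|
| 0.002 | 1.33 | 1.33 | 1.33 |
| 0.002 | 2.0 | 1.32 | 1.35 |
| 0.004 | 1.33 | 1.32 | 1.33 |
| 0.004 | 2.0 | 1.31 | 1.38 |
| 0.01 | 1.33 | 1.32 | 1.33 |
| 0.01 | 2.0 | 1.29 | 1.44 |

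The loss is small when the factor acts equally on fatal and non-fatal events, and larger when it acts more on fatal ones.

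**5. Could an effect reverse?** In the same model, bringing the five-year ratio down to 1 needs a hazard ratio for such death of about 57, 23 and 12 at d = 0.002, 0.005 and 0.01. At ten years it needs about 27, 12 and 6.

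**6. Calibration.** SCORE predicts fatal cardiovascular disease only. The planned composite holds angina, atrial fibrillation and transient ischaemic attack, and omits some fatal events. Framingham, REGICOR and DORICA predict fatal or non-fatal coronary disease. The composite omits some coronary deaths and adds non-coronary events. The mismatch therefore runs in both directions, and its net sign cannot be fixed from the article.

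**The case against.** The strongest reply is that the cumulative incidence of a first listed event, with death before it as a competing event, is a valid estimand. On that view nothing is biased; the plan has merely chosen a narrower outcome. This is right as statistics, and the downward bias exists only when the figure is read as the incidence of all cardiovascular disease. That is, however, how the objectives present it, and every score under test has a target that includes fatal events.

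A second reply is that the article says death, not death from any cause, and that assignment rules or cause-of-death data may sit in the full protocol or in Additional file 1, which is not shown. Whether cause of death is collected cannot be judged here. The event list and the state structure are both stated outright, though, and together they lead to the classification described.

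A third reply concerns size. Whether the 22.2% already contains cardiovascular deaths depends on an earlier report on this cohort that is not at hand. This stands, and it limits any numerical claim.

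A reader might also infer that fatal disease, and so SCORE's target, is wholly absent from the observed outcome. The documents do not support that, because documented fatal infarctions, strokes, heart failure and ventricular tachycardia enter through their components, as do deaths after an earlier listed event. Nor do they support the inference that effects could change sign: the hazard ratios needed in step 5 are extreme for most of the range.

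**Conclusion.** The concern holds for one group: cardiovascular deaths with no documented listed event. The plan counts them as competing. The consequences are an incidence that is too low as a measure of all post-transplant cardiovascular disease, attenuated effects for factors linked more strongly to fatal disease, a nomogram that inherits both, and distorted observed-to-predicted comparisons.

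The size is not known. An addition of 1 to 5 percentage points to the 22.2% rests on two assumptions: the rate of such deaths, and their absence from the cited figure. The attenuation in step 4 rests on assumed hazards and shows direction and order of magnitude only. The omission itself can be read directly from the text. The sample size is unaffected. This is an inexpensive improvement to the primary outcome definition, not a fault that invalidates the design.

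**What to change.** - In the Abstract and in Measurements, add cardiovascular death, including sudden cardiac death, to the event definition.
- In Statistical analysis, restrict the competing death state to non-cardiovascular death.
- State how deaths of unknown cause are classed, and repeat the primary analysis with all of them counted as cardiovascular and with none so counted.
- Calibrate each score against its own endpoint: fatal cardiovascular disease for SCORE; fatal or non-fatal coronary disease for Framingham, REGICOR and DORICA. This is needed in addition, since widening the composite does not bring it into line with SCORE.

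The cost is coding cause of death from the hospital records that the Discussion already names as the main source. Enrolment runs back to 1981, so some older deaths will have an uncertain cause; the two-way analysis shows how much that matters. No further patients are needed.

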This project was designed with three main objectives: firstly, to determine the incidence of post-transplant cardiovascular events after renal transplantation and related factors; secondly, to examine the ability of established cardiovascular risk scores (Framingham, Regicor, SCORE, and DORICA) to predict post-transplantation cardiovascular events in renal transplant recipients; and finally, to develop and validate a cardiovascular risk score to predict the risk of developing a cardiovascular event after kidney transplantation.

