### Sample size

During the study period (1981-2008) n = 2059 kidney transplants were performed in the A Coruña Hospital, corresponding to 1794 patients.

This sample size will make it possible to detect as significant, in a Cox regression model, a relative risk of 1.33 or more associated with a prevalence of exposure to a cardiovascular risk factor of 50% and a censored data percentage of 78% (Security: 95%; Statistical power: 80%). Assuming an exposure prevalence of 50% maximizes the sample size necessary to detect a relative risk of this magnitude. According to previously published data for this cohort of patients, the estimated incidence of CVD at five years is 22.2% [47], and so the censoring value was estimated at 78%. In this situation, the sample size required to estimate a relative risk of 1.33 or more (α = 0.05, β = 0.2) would be n = 1755 patients.

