## Discussion

In recent years, several important changes have occurred in the management of kidney transplant patients that have been associated with an improvement in rejection rates and early graft survival [53]. Therefore, attention is now focusing on improving long-term transplant outcomes [3]. Renal dysfunction and increased cardiovascular risk are some of the factors that have a negative impact on long-term graft and patient survival. Although some authors have documented a reduction in CVD-related deaths in kidney transplant recipients in recent years, CVD is still the leading cause of death in patients with a functioning allograft [2].

Several studies have analyzed the risk factors connected with the incidence of cardiovascular events after kidney transplantation [4-29]. However, the role of some novel risk factors remains unclear. Furthermore, most of the previous studies are based on retrospective analyses of registry data, which contains information only on baseline data at the time of transplantation and the immediate post-transplantation follow-up. As a result, long-term follow-up data on clinical, biochemical and treatment covariates after transplantation is not always available.

This study will allow us to determine the post-transplant incidence of cardiovascular events in a cohort of renal transplant recipients in Spain, as well as to confirm the relationship between some CVD risk factors and the occurrence of a cardiovascular event in these patients. The development of a specific CVD risk score for kidney transplant recipients would make it possible to identify patients at high risk for coronary events at the time of transplantation, or shortly after the transplant. Therefore, this risk assessment could be used to recommend lifestyle changes for patients, to initiate appropriate treatment, or to redesign the immunosuppressive regimens for the prevention of primary or recurrent cardiovascular events in kidney transplant patients. The majority of studies use survival analysis strategies with the methodology of Kaplan and Meier. As this methodology may lead to overestimating the likelihood of the occurrence of the events of interest, we propose a competitive risk analysis in order to study the prognosis of these patients [48,49].

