One of the limitations of this study is that information will mostly be taken retrospectively from hospital records, which could lead to information bias. On the other hand, transplant recipients are subjected to a more exhaustive follow-up than normal, not only during the immediate post-transplant period, but also during the years after the transplant. This fact would minimize any possible information bias. Likewise, during the study period standard immunosuppressive therapy has changed, and the treatment for each patient will depend on the date of transplantation and other medical subjective criteria. In order to control the changes that have occurred over the years, adjustments will be made based on the year of transplantation. Also, the therapeutic changes that occurred during the follow-up period for each of the patients will make it difficult to establish relationships between the medication and the cardiovascular events. Therefore, the impact of immunosuppressant medication on the presence of cardiovascular events in the follow-up could not be well established. The role of immunosuppressant agents must be investigated in greater detail with randomized clinical studies, and not with observational studies of this kind. However, our study will include a large cohort of patients with a long follow-up period, and the sample size is expected to be large enough both to identify individual CVD risk factors from multivariate analysis and to develop a new CVD prediction model.

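### Fine-Gray is the only regression model named, but the aim of identifying individual CVD risk factors also needs cause-specific hazard ratios

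*Protocol article*

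**What the plan says.** All of this is in the protocol article.

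- **Model.** Statistical analysis: "The cumulative incidence function regression model of Fine and Gray will be used for multiple regression analyses". Groups are compared by cumulative incidence functions. Patients fall into four states: functioning graft, death, graft failure and CVD. No cause-specific hazard model is named, and no regression for death or graft failure.
- **Primary outcome.** The same section defines it as "estimation of the probability of cardiovascular disease in the presence of other competitive events in renal transplant patients". A nomogram follows from the competing-risks analysis.
- **Risk-factor aim.** The first objective, at the end of the Background, is "to determine the incidence of post-transplant cardiovascular events after renal transplantation and related factors". The Discussion expects the study "to confirm the relationship between some CVD risk factors and the occurrence of a cardiovascular event in these patients" and considers the sample large enough "to identify individual CVD risk factors from multivariate analysis".
- **Sample size.** The calculation is for another model: "This sample size will make it possible to detect as significant, in a Cox regression model, a relative risk of 1.33 or more".
- **Follow-up.** The Measurements section follows patients from transplantation until they die or return to dialysis. Transplants date from 1981 to 2008.

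**The concern.** The plan asks two questions. One is how likely a recipient is to have a CVD event, given that death or graft loss may come first. The other is which factors are related to CVD. Fine-Gray answers the first. For the second it gives an ambiguous answer: patients who die or lose the graft stay in the subdistribution risk set, so a factor that acts only on those events still moves the ratio for CVD.

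This matters for the factors under study. The Background lists prior dialysis duration, graft function, proteinuria and acute rejection as candidates, and the Discussion itself says that renal dysfunction worsens graft and patient survival. A factor that raises both CVD and graft loss or death would have its CVD association understated. A factor that raises only the competing events could appear mildly protective. Readers of the final report could then misjudge which factors drive CVD, although the Fine-Gray model had been fitted correctly.

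The Discussion justifies competing-risk methods by the overestimation of event probability with Kaplan-Meier. That supports cumulative incidence for absolute risk. It does not support the subdistribution ratio as the sole measure of association.

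**Working it through.** **1. The plan's own figure.** Inputs from the Sample size section: relative risk 1.33, 50% exposed, 78% censored, power 80%, α = 0.05 (two-sided according to Statistical analysis).

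- Events for a Cox model with a binary covariate (Schoenfeld): (1.960 + 0.842)² / [0.5 × 0.5 × (ln 1.33)²] = 7.849 / (0.25 × 0.08133) = 386.0.
- Patients: 386.0 / 0.22 = 1754.7, which rounds up to the stated 1755.
- With 1794 patients: 1794 × 0.22 = 394.7 events. Power = Φ(√(394.7 × 0.25) × 0.2852 − 1.96) = Φ(0.87), about 81%.

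The figure is reproduced. When patients with competing events are censored, the parameter of that Cox model is the cause-specific hazard ratio.

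**2. From hazards to the subdistribution ratio.** With constant hazards λ₁ (CVD) and λ₂ (death or graft failure), the cumulative incidence of CVD is

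F(t) = λ₁/(λ₁+λ₂) × [1 − exp(−(λ₁+λ₂)t)], with density f(t) = λ₁ exp(−(λ₁+λ₂)t).

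The subdistribution hazard is f(t)/[1 − F(t)]. With exposure proportion p and censoring only at a fixed time T, the Fine-Gray ratio θ solves

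∫₀ᵀ { p f₁ − [p f₁ + (1−p) f₀] × pθ(1−F₁) / [pθ(1−F₁) + (1−p)(1−F₀)] } dt = 0,

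where subscripts 1 and 0 denote exposed and unexposed.

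**3. Inputs.**

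- From the document: 5-year CVD incidence of 22.2%, giving λ₁ = −ln(1 − 0.222)/5 = 0.0502 per year; exposure 50%; planned effect 1.33.
- Assumed, not in the document: constant hazards; λ₂ = 0.04 or 0.06 per year in the unexposed, doubled by the factor; administrative censoring only.

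**4. Results** (λ₂ = 0.04 / 0.06).

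| Horizon | Cause-specific HR 1.00 | Cause-specific HR 1.33 |
|---|---|---|
| 5 years | 0.91 / 0.87 | 1.20 / 1.15 |
| 10 years | 0.83 / 0.77 | 1.09 / 1.01 |
| 15 years | 0.78 / 0.71 | not needed for the point |

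**5. Sensitivity to calibration.** The value 0.0502 treats 22.2% as if there were no competing events. With λ₂ = 0.04 it gives F(5) = 0.0502/0.0902 × (1 − e^(−0.451)) = 20.2% in the unexposed, slightly below 22.2%. A second set of runs therefore fixed the unexposed 5-year CVD incidence at 22.2% and assumed a 5-year competing incidence of 10%, 20% or 30%, with the competing hazard again doubled.

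| Horizon | Cause-specific HR 1.00 | Cause-specific HR 1.33 |
|---|---|---|
| 5 years | 0.94, 0.88, 0.83 | 1.25, 1.17, 1.09 |
| 10 years | 0.89, 0.80, 0.72 | 1.17, 1.04, 0.94 |

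If the factor triples the competing hazard and the competing incidence is 30%, a true 1.33 becomes 0.91 at 5 years and 0.72 at 10. In both calibrations the shift is downward and grows with follow-up.

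**The case against.** **Fine-Gray matches the declared primary outcome.** This stands. Cumulative incidence, ARR, NNT and the nomogram are all absolute-risk quantities. One could also read the related factors in the first objective as factors associated with that absolute incidence. The Discussion goes further, however, and speaks of confirming relationships and identifying individual risk factors. The one limit it draws on such inference concerns immunosuppressants.

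**Nothing excludes other models.** This is true. The article is condensed, and the Sample size section mentions Cox regression. The point is therefore that Fine-Gray is the only regression model named for the analysis, not that others are ruled out. The Statistical analysis section still assigns multiple regression to it without qualification.

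**The distortion may be small.** Over 5 years it is modest, and its size rests on competing rates that the document does not give. Long follow-up is possible for the earlier transplants, so the 5-year figures need not be the relevant ones.

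**Stronger readings that a reader might infer.**

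- *True risk factors will look protective.* This is the extreme case. It requires little or no effect on the CVD hazard, or high competing rates with long follow-up. The Background presents dialysis duration, rejection and graft function as factors that seem to raise CVD, so attenuation is the likelier result.
- *A false protective finding has a known high probability.* Ratios of about 0.78 to 0.71 belong to some 15 years of follow-up, when these inputs imply roughly 570 to 670 events. The count of about 395 is a 5-year figure. Combining the two mixes horizons, so no such probability is offered here.
- *The sample size is wrong because it uses Cox.* It reproduces, and an event-based Cox formula is a common planning approximation.

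**Conclusion.** The point holds as a recommended improvement; it does not make the primary analysis wrong. Fine-Gray is right for the probability of CVD and for the nomogram. Used alone, it is a poor basis for statements about which factors are related to CVD, because its ratio also carries effects on death and graft failure.

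The direction is secure: a factor that raises the competing hazard pulls the subdistribution ratio below the cause-specific one. The size is illustrative. It rests on constant hazards, assumed competing rates, a doubled competing hazard, 50% exposure and administrative censoring only, and it depends strongly on length of follow-up. Under these assumptions the planned detectable effect of 1.33 shrinks to between 1.25 and 1.09 at 5 years across both calibrations. At 10 years it lies between 1.17 and 0.94, so a real risk factor could be missed.

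**What to change.** In Statistical analysis, add cause-specific Cox models for CVD, for death and for graft failure, with the same covariates. Report their hazard ratios beside the Fine-Gray results, and state that conclusions about risk-factor associations rest on the cause-specific ratios. Keep Fine-Gray and cumulative incidence functions for absolute risk and the nomogram.

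The models for death and graft failure show readers why the two ratios for CVD differ when they do. Cause-specific ratios remain observational, so confounding still has to be considered.

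The cost is a few more models on the same data and one more results table. No new sample size is needed, because the existing calculation already describes a Cox model.
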